#### Secondary outcomes

##### Affective exercise experiences

To measure affective experiences associated with past exercise participation, we use the AFFEXX questionnaire [9], which was translated and validated in German by Brand et al. [89]. The questionnaire assesses the following main areas: (1) three core affective experiences — pleasure vs. displeasure, energy vs. tiredness, and calmness vs. tension; (2) six emotional-antecedent appraisals — Liking vs. Disliking exercise in groups, Showing off vs. Shying away, Physical Empowerment vs. Bodily Harm, Pride/Honor vs. Shame/Guilt, Competence vs. Incompetence, and Interest vs. Boredom; and (3) the motivational tendency toward attraction to or avoidance of exercise (Attraction vs. Antipathy). The instrument consists of 36 bipolar items rated on a Likert scale, with antithetically worded statements ranging from 1 (e.g., “exercise makes me feel worse”) to 7 (e.g., “exercise makes me feel better”). The German translation demonstrated good to excellent internal consistency for all subscales (α = 0.80–0.90; 89). For our analysis, we will use mean scores for all subscales.

##### Motivational competence

We assess motivational competence with a scale developed and validated by Schorno et al. [90]. Participants must rate four statements (e.g., “I know exactly what to look for in an exercise activity so that I will enjoy it.” or “I know what experiences to expect with different types of exercise activities.”) on a 5-point Likert scale ranging from 1 (does not apply at all) to 5 (applies exactly). The scale demonstrated good internal consistency in existing studies (24, 86; α = 0.86). We will use the sum of the four items for further analysis.

##### Exercise behavior

Exercise behavior is measured in two ways: First, we assess the actual exercise volume with the Physical Activity, Exercise, and Sport Questionnaire (BSA-F; ([81]). Participants must report up to three exercise or sport activities they engaged in over the past four weeks, including the frequency and duration of each activity. Using this data, the weekly volume of exercise and sport (in minutes) will be calculated. The questionnaire has demonstrated satisfactory validity, as evidenced by its correlation with aerobic fitness [81]. Secondly, we assess the habitual volume of leisure-time PA with the Physical Activity Questionnaire (EHIS-PAQ; [91]). We use seven items to assess PA during transportation and during leisure time, including sports activities, aerobic health-enhancing activities, and muscle-strengthening activities in a typical week. The EHIS-PAQ demonstrates acceptable reliability and moderate to strong validity across all domains except for moderate-to-vigorous PA [99]. For our analysis, we will compute the conservative Health-Enhancing Physical Activity (HEPA) Index, which combines data on transportation-related PA (excluding walking) and leisure-time PA to evaluate compliance with the aerobic PA guidelines [91].

##### Habitual affective well-being

To assess well-being, we use the German version of the World Health Organization-Five Well-Being Index (WHO-5; [92]). It consists of five statements relating to the past two weeks (e.g., “I have felt calm and relaxed.”). Participants must rate each statement on a scale ranging from 0 (at no time) to 5 (all of the time). The scale has an excellent internal consistency with Cronbach’s α = 0.92. For our analysis, we will use the mean score of all five items.

#### Potential confounding variables and control variables

##### Body mass index (BMI)

We assess body weight and height through self-reports and subsequently use this data to calculate the BMI.

##### Education level

To assess the formal education level, participants report their highest educational qualification based on six categories. We will code the responses according to the International Standard Classification of Education (ISCED) to ensure international comparability.

##### Participants’ sympathy and perceived competence of instructors

As a potential control variable, we assess participants'sympathy toward the instructor using a subscale of the German version of the Leader-Member Exchange Scale (LMX-MDM; [93]), which has been slightly adapted for the PA setting. This subscale consists of three items rated on a 7-point Likert scale. Additionally, we measure participants'perceptions of the instructor's motivational, adaptive, and organizational competencies using a questionnaire developed by Strauch et al. [94]. This questionnaire comprises three items for each of the three subdomains, also rated on a 7-point Likert scale.

##### Perceived fitness

We measure perceived physical fitness with a modified version of a subscale from the adjective list for assessing perceived physical state (PEPS; [95]). The subscale includes four items rated on a 6-point Likert scale.

##### Movement competence, control competence for physical training, and PA-specific self-control

We assess three additional facets of PA-related health competence using scales developed from the PAHCO questionnaire [13]. The scales comprise three items for PA-specific self-control, five items for movement competence, and six items for control competence in physical training. All items are measured on a 5-point Likert scale.

#### Implementation outcomes

##### Satisfaction, acceptability, appropriateness, and feasibility of the programs

To assess participants’ satisfaction with the exercise programs, we employed a single-item question with a 5-point Likert scale [100]. To measure the acceptability of intervention measure (AIM), intervention appropriateness measure (IAM), and the feasibility of intervention measure of the exercise programs (FIM), we use two items per subdomain of the German versions of the implementation outcome measures [96], also rated on a 5-point Likert scale. Additionally, semi-structured interviews will be conducted with participants from the IG after program completion. These interviews aim to provide deeper insights into participants’ experiences and perspectives on the FEEL program.

##### Treatment fidelity

We measure treatment fidelity with standardized notation sheets for each session of the exercise programs. Instructors document any deviations from the intended program delivery.

##### Attendance rate and reasons for absences

The number of attended sessions is documented by the instructors. Furthermore, we ask participants to retrospectively specify their reasons for their (potential) absences from the sessions using a self-developed open-ended question.

##### Delivered content and learning experiences in the exercise programs

To assess which contents participants perceived and the learning experiences they gained in the exercise programs, we developed items based on a previous study [97]. The 16 items are rated on a 5-point Likert scale.

##### Experiences with (re-)adopting and resuming exercise in the programs

Guided semi-structured interviews are conducted by researchers with participants and program dropouts. These interviews offer insights into individuals'experiences of (re)entering exercise and examine the facilitators and barriers they encounter.

#### Data management and monitoring

Participants complete the surveys online via the LimeSurvey.org platform, with data collection separated for the two study sites. Data is downloaded from the platform, and each participant's responses are linked through a unique code. Interviews with program participants and dropouts are audio-recorded and transcribed verbatim, with all personal data anonymized during transcription. Instructors maintain attendance lists and notation sheets after each course session.

All collected data, including survey responses, audio recordings, transcripts, and instructor documents, is stored on password-protected servers at the respective universities. After data collection is completed, datasets from both sites are merged using anonymized participant information.

### Statistical analysis

To test the hypothesis, we will use multilevel modeling to examine the treatment effects on the primary outcome (PAAR) and the secondary outcomes (affective exercise experiences, motivational competence, exercise behavior, habitual affective well-being). Each outcome will be modeled as a function of group (IG vs. CG), time (t1, t2, t3), and their interaction.

To account for the stratified randomization by study site, the study site will be included as a covariate in all analyses. Besides baseline BMI, education level, the instructors' sympathy, and perceived competence will also be evaluated as potential covariates, as they may influence the primary outcome [101]. Covariates with a significant influence on the primary outcome will be included in the analyses.

All analyses will adhere to a modified intention-to-treat (mITT) approach, excluding participants who never attended a single session. As a sensitivity analysis, we will separately evaluate participants with an attendance rate of at least 50%. Multiple imputation methods will be applied to address missing data due to dropout or non-contribution to primary outcome measurements.

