## Methods

### Design

The FEEL study is a cluster randomized controlled trial with an IG (exercise program: FEEL) and active CG (exercise program: Functional Training) with three points of assessment (t1: pre, t2: post, t3: follow-up). We designed the study to investigate the superiority of the intervention condition to the control condition from an efficacy perspective [77]. Participants are allocated to each condition in a 1:1 ratio. The FEEL and Functional Training programs are both carried out in courses over eight consecutive weeks with one 90-min session per week in groups of approximately 12–15 people but have different thematic and methodological focuses. As the FEEL study is a cooperation project between the University of Bern, Switzerland, and the University of Tübingen, Germany, the multicenter study is conducted at these two sites from September 2024 to August 2025 in at least three study waves, with a total of 160 participants. We registered the trial on https://drks.de with ID number DRKS00035302 and received approval from the local ethics committees at the University of Tübingen, Germany (ID: A2.5.4–334.1_hb) and the University of Bern, Switzerland (ID: 2024–02-06). With the present study protocol, we adhere to the Standard Protocol Items: Recommendations for Intervention Trials (SPIRIT) guidelines [78] and aligned it with the Template for Intervention Description and Replication (TIDieR) Checklist and Guide [79].

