### Sample size

We conducted the sample size calculation a priori to the main study using the powerlmm package in R (Version 4.2.2). Based on prior research [14, 20, 87, 88], we assumed an effect size of *d* = 0.5 for differences in PAAR (primary outcome) between the IG and the CG over time (t1, t2, t3), with a statistical power of ≥ 80% and a two-sided significance level of α = 0.05. Additionally, we set the baseline intraclass correlation coefficient (ICC) to ICC = 0.5 and the random slope variance to 0.02. We anticipated a dropout rate of 20% at both after t1 and after t2. Accordingly, the calculation determined a minimum required sample size of N = 160 participants.

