### Randomization

Cluster randomization occurs four weeks before the course begins (see Fig. 5) for practical reasons: the FEEL and Functional Training programs require indoor spaces in municipal or university halls, which are in high demand. The courses are scheduled at fixed times during each wave, and instructors must be available at these times.

The cluster randomization is conducted separately for the two study sites. This stratification ensures that the courses within each study site are evenly distributed between IG and CG. The assignment of course time A and course time B to either the intervention or control condition is determined by a computerized random number generator (random.org) operated by a researcher not involved in the project. We apply an equal allocation ratio of 1:1, meaning there is a 50% probability that either course time A or B will be assigned to the intervention, with the other time allocated to the control condition.

Table 2 shows the planned allocation of the study groups. We expect an average group size of 12 participants. This leads to a slightly larger total sample size than the required *N* = 160 participants (see section on sample size above).

**Table 2 Tab2:** Planned allocation of the study groups

	Total	Wave 1						Wave 2				Wave 3			
Course clusters	7	A1		B1		B2		A2		B3		A3		B4	
Course allocations (ratio: 1:1)	14	IG	CG	IG	CG	IG	CG	IG	CG	IG	CG	IG	CG	IG	CG
Expected n		12	12	12	12	12	12	12	12	12	12	12	12	12	12
Sum n	168	24		24		24		24		24		24		24	

A = study site A, B = study site B, *IG* intervention group, *CG* control group

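### Treating t1 as a free outcome occasion makes the group-by-time test a change-from-baseline comparison: valid, but less precise than using the t1 value already collected

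*Protocol article*

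**What the plan says.** The Statistical analysis section sets one model form for the primary outcome (PAAR) and all secondary outcomes: "Each outcome will be modeled as a function of group (IG vs. CG), time (t1, t2, t3), and their interaction". Site is a fixed covariate. BMI, education and the participants' ratings of the instructor are candidate covariates. Baseline PAAR is not named as a covariate, and a common t1 mean is not stated. Table 3 shows that PAAR is measured at t1, t2 and t3.

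The Sample size section assumes d = 0.5 for PAAR, "with a statistical power of ≥ 80% and a two-sided significance level of α = 0.05". It adds "we set the baseline intraclass correlation coefficient (ICC) to ICC = 0.5 and the random slope variance to 0.02" and "We anticipated a dropout rate of 20% at both after t1 and after t2", and concludes that "the calculation determined a minimum required sample size of N = 160 participants". Under Randomization, Table 2 plans 14 courses, and "We expect an average group size of 12 participants".

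**The concern.** A group main effect together with a group-by-time interaction leaves the arms free to differ at t1. The interaction then compares each arm's movement away from its own t1 mean. At a correlation of 0.5 the change score has variance 2(1 - 0.5) = 1 in units of the outcome variance, which is no better than comparing follow-up scores and ignoring t1. A baseline-adjusted comparison has variance 1 - 0.5² = 0.75.

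At stake is precision that the trial has already paid for. The article hypothesises higher PAAR both directly after the programme and at follow-up, and t3 is where dropout is heaviest.

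**Working it through.** **Inputs.** From the article: N = 160 with 1:1 allocation (80 per arm), d = 0.5, two-sided α = 0.05, ICC 0.5, slope variance 0.02, 20% dropout after t1 and 20% after t2, 12 per course.

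Assumptions made here:
- d is in baseline SD units, and the ICC is the within-person correlation.
- The slope variance is either a ratio to the error variance of 0.5 (giving 0.01) or an absolute 0.02 with total variance 1.
- Loss at t3 is 20% (cumulative reading), 36% (1 - 0.8²) or 40% (additive).

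**The plan's own figure.** With change-score variance 1, n per arm = 2(1.96 + 0.84)²/0.5² ≈ 63, so 126/0.8 ≈ 158. A mixed model with free t1 means gives 158 (slope variance 0.01) or 164 (0.02) when 20% are missing at both t2 and t3. So 160 is reproduced under the cumulative reading. With successive or additive losses the same model needs 184-202, and power at 160 is 0.70-0.75.

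**Equivalence to change.** With complete data and no random slope, the interaction variance is 0.025. A difference in mean change has variance 2 × 2(1 - 0.5)/80 = 0.025. The two are identical.

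**Two-occasion formula.** Let f be the fraction missing at follow-up and ρ the correlation. In units of 2/n:
- common t1 mean: a = (1 - ρ²)/(1 - f)
- free t1 means: u = a + (1 - ρ)²
- reduction = (1 - ρ)²/u

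| ρ | f | a | u | reduction |
|---|---|---|---|---|
| 0.5 | 0 | 0.750 | 1.000 | 25% |
| 0.5 | 0.20 | 0.938 | 1.188 | 21% |
| 0.5 | 0.36 | 1.172 | 1.422 | 18% |
| 0.5 | 0.40 | 1.250 | 1.500 | 17% |
| 0.7 | 0 | 0.510 | 0.600 | 15% |
| 0.7 | 0.40 | 0.850 | 0.940 | 10% |
| 0.3 | 0 | 0.910 | 1.400 | 35% |
| 0.3 | 0.40 | 1.517 | 2.007 | 24% |

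**Three-occasion model with the random slope, N = 160, losses 20% then 36%.** Power ≈ Φ(0.5/SE - 1.96).

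| Slope variance | Time | SE free → common | variance | power |
|---|---|---|---|---|
| 0.01 | t2 | 0.173 → 0.154 | -21% | 82% → 90% |
| 0.01 | t3 | 0.191 → 0.174 | -17% | 75% → 82% |
| 0.02 | t2 | 0.174 → 0.155 | -21% | 82% → 90% |
| 0.02 | t3 | 0.194 → 0.178 | -17% | 73% → 80% |

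Across the three dropout readings the reduction at t3 runs from 16% (40% missing, slope variance 0.02) to 20% (20% missing, slope variance 0.01), or 21% with no random slope.

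**Course effects.** The article gives no course ICC, so c is assumed. Take total variance 1, correlation 0.5 including a stable course share c, 12 per course and complete data. The variance of a course mean is A = (1 - c)/12 + c. The covariance of its t1 and follow-up means is B = (0.5 - c)/12 + c. Change: 2(A - B) = 0.0833, whatever c is.
- Common t1 mean with course effects at all occasions, A - B²/A: 0.0699 at c = 0.05 (-16%) and 0.0734 at c = 0.10 (-12%).
- Individual t1 covariate only, slope 0.5, 1.25A - B: 0.0740 at c = 0.05 (-11%), 0.0808 at 0.08 (-3%) and 0.0854 at 0.10 (+2.5%).

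If the course effect instead arises after t1, the reduction is (1.00 - 0.75)/12 divided by (1.00/12 + c): 16% at 0.05 and 11% at 0.10.

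**The case against.** The strongest reply is that nothing here is wrong. The planned model is valid, it matches the way the trial was sized, and a condensed article may leave the treatment of t1 means to a fuller plan. A reader might infer bias or an invalid test; the documents do not support that. What stands against the reply is that the article does state the model and its covariates, and the natural reading leaves t1 means free.

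A reader might also infer that there is no reason to allow a baseline difference. That is too strong:
- Under Randomization, courses are allocated four weeks before they start. Under Procedure, registration stays open until the second session, participants choose a course time, and staff may move them.
- Some t1 forms may be completed after the first session.
- The analysis set drops people who never attended.

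Equal expected baselines therefore rest on randomization plus the blinding of participants to course content. Late t1 values disturb the change analysis too.

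A third tempting inference is that any baseline adjustment guards against chance imbalance between 14 courses. Stable course differences cancel in change scores, but an individual t1 covariate with slope near 0.5 leaves about half of them. As shown above, its advantage is gone by a course ICC of about 0.08-0.10. This part of the objection stands and shapes the fix.

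Finally, the gain is not uniform across outcomes. Motivational competence has no t3 measurement in Table 3. Weekly exercise volume (BSA-F) should be near zero at t1 because eligibility excludes regular exercisers, so little gain is expected there.

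**Conclusion.** The point holds as a loss of efficiency, not a bias. At a correlation of 0.5 and no course effect, the planned contrast has avoidable variance of about 21% at t2 and 16-21% at t3 under the stated dropout, and 25% with complete data and no random slope. This does not show that the trial is underpowered: the t3 power of 73-75% depends on reading the dropout as two successive losses, whereas N = 160 is reproduced under a 20% cumulative loss. Nor is the percentage fixed. It falls to about 10-15% at a correlation of 0.7 and rises to about 24-35% at 0.3. It is about 12-16% at an assumed course ICC of 0.05-0.10 if course is modelled at all occasions. The gain stays positive in every case examined with that model. The change is worth making.

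**What to change.** For PAAR, make the primary analysis a constrained longitudinal multilevel model: t1, t2 and t3 as outcomes, one common t1 mean for both arms, and course random effects that include the t1 occasion. An alternative is to model t2 and t3 with both the individual t1 value and the course-mean t1 value as covariates. Report the adjusted group differences at t2 and t3.

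Apply the same form to the other roughly continuous outcomes at the times they are measured (motivational competence at t2 only). Keep the unconstrained group-by-time model as a sensitivity analysis. Flag t1 questionnaires completed after the first session.

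The cost is a few sentences of model wording, with no added participants, visits or questionnaires. Record the change, with its date, before the blinded statistician learns the allocation. The small downside is the common-baseline assumption, which relies on participant blinding because registration stays open after courses are randomized; the sensitivity analysis shows how much depends on it. A missing t1 value is handled by the constrained model or by the multiple imputation already planned.

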### Key element 1: Socially enriched exercise setting

A group exercise setting and the norms established within it can significantly influence participants' affective responses [28]. Especially in a society where exercise is increasingly framed as a moral obligation, physical inactivity and low fitness levels are often linked to personal irresponsibility or may lead to diminished self-worth [29]. For instance, group exercise norms (e.g., appearance-focused language) may provoke feelings of embarrassment or discomfort driven by concerns about social perception and self-presentation [30, 31]. To mitigate these negative effects, it is essential to intentionally design exercise spaces that shield individuals from adverse (self-) evaluations [32] and actively promote group cohesion [33]. Moreover, the sometimes negative attitudes of instructors toward inactive individuals can be adjusted through intense empathy-evoking exercises [34] to create a more welcoming and socially enriched instructor behavior [35–38].

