#### Training of the program instructors

We provide training for instructors of both the FEEL and the Functional Training program. These trainings cover overarching aspects such as the program objectives and structure. Additionally, we review the individual course sessions by discussing their topics, main goals, exercise types, and additional content. Finally, we introduce instructors to the program manual and demonstrated selected content through practical examples. For FEEL program instructors, a supplementary workshop focuses on fostering a socially enriched exercise setting (key element 1; see Appendix 3 for further information).

After the initial training, we provide ongoing coaching throughout the program. For the FEEL program, we meet with instructors to discuss every course session in advance. For the Functional Training program, we schedule coaching sessions ahead of the third and sixth-course sessions. Regardless of the program, all instructors can reach out to one of the principal investigators at any time during the course period to ask questions or address issues as part of our troubleshooting support.

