***Potential confounding variables and control variables***						
Body-Mass-Index		Self-reported height and weight		x		
Education level		List of highest formal education		x		
Participants sympathy and perceived competence of instructors		Subscale from LMX-MDM [93]			x	
		Questionnaire to assess instructor’s motivational, adaptive, and organizational competencies [94]			x	
Perceived fitness		Subscale from PEPS [95]		x	x	x
Movement competence		Subscales from the PAHCO-questionnaire [13]		x	x	x
Control competence for physical training				x	x	x
PA-specific self-control				x	x	x

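### Instructor ratings taken only at t2 can enter the efficacy models through a significance rule, although allocation can change them; this may remove part of FEEL's effect

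*Protocol article*

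**What the plan says.** The Statistical analysis section models each outcome on group, time (t1, t2, t3) and the group-by-time interaction, with study site as a fixed choice of covariate. Beside baseline BMI and education level it adds that "the instructors' sympathy, and perceived competence will also be evaluated as potential covariates, as they may influence the primary outcome". The rule for entry is "Covariates with a significant influence on the primary outcome will be included in the analyses".

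In Table 3, BMI and education are marked at t1. The row "Participants sympathy and perceived competence of instructors", under potential confounders and control variables, is marked at t2 only for both instruments. The measures section makes clear that each person rates the instructor of their own course: "Additionally, we measure participants'perceptions of the instructor's motivational, adaptive, and organizational competencies".

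Three other places bear on whether allocation can move these ratings:

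- Key element 1 of FEEL aims "to create a more welcoming and socially enriched instructor behavior".
- Under Training of the program instructors: "For FEEL program instructors, a supplementary workshop focuses on fostering a socially enriched exercise setting". FEEL instructors are also coached before every session, control instructors before the third and sixth sessions.
- Under Instructors' eligibility, FEEL instructors are mainly project members and control instructors are recruited externally.

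The closing part of the Background states the primary hypothesis as higher PAAR scores in the intervention group directly after the programme and at follow-up. The Abstract names group-by-time interactions as the object of the analysis. Missing data are to be handled by multiple imputation.

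**The concern.** A variable that allocation can change is not a confounder of a randomised comparison. Adjusting for it replaces the question of whether FEEL beats Functional Training with a partial direct effect that leaves out whatever runs through the instructor. It can also bring in bias from any unmeasured trait that drives both the rating and PAAR. By the article's own description, the instructor is one of the routes through which FEEL is meant to work.

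The selection rule is a second fault. It covers BMI and education as well, and it stands even if FEEL leaves the ratings untouched: whether a covariate enters the primary model depends on its relation to the outcome in the same trial data.

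**Working it through.** **1. The plan's own figure.** With d = 0.5, two-sided α = 0.05 and 80% power, a comparison of two means needs 2 × (1.960 + 0.842)² / 0.5² = 62.8, so 63 per arm and 126 in total. Allowing for 20% dropout, 126 / 0.8 = 157.5, so 158. A linear growth model with the stated ICC of 0.5 and slope variance of 0.02, with the same 20% missing at t2 and t3, gives 156. Both agree with N = 160 on that reading of the dropout assumption. The target effect of 0.5 SD is the reference below.

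**2. Assumptions not in the documents.** Let *a* be the arm difference in the rating (in SD) caused by FEEL, and *b* the change in later PAAR (in SD) per SD of rating. The true total effect is 0.50 SD at t2 and t3, of which *a* × *b* runs through the rating.

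**3. What adjustment does, by model form.**

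- *Rating by time:* the group-by-time effect becomes 0.50 − *a* × *b*.
- *Rating as a main effect, complete data:* the rating has one value per person, so it cancels from within-person change and group-by-time stays at 0.50. The fitted slope is the average over the three visits, (0 + *b* + *b*)/3 = 2*b*/3. The group contrast at t2 therefore becomes 0.50 − 2*ab*/3, and a false baseline difference of −2*ab*/3 appears.

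| *a* | *b* | Group-by-time, rating by time | Group-by-time, main effect | t2 contrast, main effect |
|---|---|---|---|---|
| 0 | any | 0.50 | 0.50 | 0.50 |
| 0.3 | 0.2 | 0.50 − 0.06 = 0.44 | 0.50 | 0.50 − 0.04 = 0.46 |
| 0.5 | 0.2 | 0.50 − 0.10 = 0.40 | 0.50 | 0.50 − 0.07 = 0.43 |
| 0.5 | 0.4 | 0.50 − 0.20 = 0.30 | 0.50 | 0.50 − 0.13 = 0.37 |
| 0.8 | 0.4 | 0.50 − 0.32 = 0.18 | 0.50 | 0.50 − 0.21 = 0.29 |

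A simulation with 200,000 participants and a random intercept agrees to within about 0.01. If the rating also correlates 0.3 with a person's stable PAAR level, the t2 contrast in the last row falls further, to 0.12.

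**4. Would the rule let the rating in?** With N = 160, complete data, *a* = 0.5 and the rating tested as a main effect at 5%, it is selected in about 53% of trials for *b* = 0.2 and 99% for *b* = 0.4.

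**5. What attenuation would cost.** With 80 × 0.8 = 64 completers per arm, a simple two-mean comparison has 81% power at 0.5 SD, 62% at 0.4 and 40% at 0.3. This ignores clustering by course.

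**6. People without a t2 form.** At 20% dropout after t1 this is 0.2 × 160 = 32, or 0.2 × 168 = 33.6 (about 34) of the allocation in Table 2. Multiple imputation keeps them, but any model containing the rating then needs an imputed opinion of an instructor they may hardly have met.

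**The case against.** The strongest defence is that the article states no covariate-by-time term. Read literally, covariates enter as main effects and the Abstract points to the interaction; in complete data that interaction does not move. This stands, and it limits the claim. It does not clear the plan, because the hypothesis concerns scores after the programme and at follow-up, and a group contrast at those visits is attenuated even by a main effect if FEEL shifts the ratings.

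A reader might infer that FEEL's effect will be cut, perhaps by 8 to 64% (*a* × *b* from 0.2 × 0.2 = 0.04 to 0.8 × 0.4 = 0.32, out of 0.50). The documents do not support that as a forecast. It needs a rating-by-time term that the article does not state, both drivers are assumed, and the upper end pairs the two largest values.

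A reader might also infer that everyone without a t2 form is lost. That would happen only in a complete-case fit, and the article plans multiple imputation.

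There is a visible reason to look at the ratings: instructor source differs by arm for reasons outside the programme content, and the rated competencies are not identical to key element 1. That justifies a labelled secondary analysis, not adjustment of the primary one.

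Finally, the statistician is blinded, and the test level and selection model may be left to an analysis plan. Blinding limits steering towards a result, but the rule as stated still makes the model depend on the outcome data. For BMI and education this is poor practice rather than post-allocation bias.

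**Conclusion.** The point holds as a fault in what the article fixes: two ratings made after eight weeks in the assigned arm may enter the efficacy models, by a rule driven by the trial outcome. Loss of effect is a risk, not a certainty. It requires FEEL to change the ratings and the ratings to relate to PAAR. Given both, contrasts at t2 or t3 are attenuated. The group-by-time term is attenuated by about arm difference × slope if the rating enters by time (0.50 to between 0.44 and 0.18 over the rows shown with *a* above 0), and is unchanged in complete data if it enters only as a main effect. The main-effect form was not checked under dropout with imputed ratings. The objection to selecting covariates by significance depends on none of these assumptions.

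**What to change.** - Remove instructor sympathy and perceived competence from the covariates of every efficacy model, primary and secondary. Keep them for an analysis labelled exploratory or mediation.
- Delete the significance rule.
- Name the adjustment set in advance: study site, as already planned, plus baseline BMI and education if wanted, included whatever their p-values.
- Do not add baseline PAAR as a covariate while t1 remains a response in the model, since it would then be both outcome and predictor.

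The cost is about two sentences in the analysis section, with no new data and no change to N = 160. The last assessments were due in late autumn 2025 and the article is dated 28 November 2025, so the documents do not show whether unblinding has taken place. If it has not, make the change as a dated amendment first. If it has, report the change as made afterwards and present the model without the ratings as primary.
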